#### Sample size calculation

Sample size calculations were performed with a power of 80% and a significance level of 5%, with a treatment difference in remission rate of at least 34%; 21% remission rate in standard of care compared with 55% in the anti-TNF treatment arm. The calculated sample size was determined to be 62 patients, with a 10% dropout allowance increasing the total trial size to 70 patients when rounded and split evenly between arms.

The Birmingham ICI-IA cohort was used to identify glucocorticoid-free remission rate in the control arm. Remission rates on treatment in inflammatory arthritis with anti-TNF vary by disease and study design. Remission rates in established RA of 47% are seen at 6 months. Factors associated with drug-free remission are absence of anti-CCP antibodies, male sex and shorter RA symptoms, all of which favour a higher remission rate in ICI-IA when compared with a RA population. ICI-IA shows greater clinical resemblance to PsA than RA and real-world remission rates in PsA are 60% and up to 81% in early PsA. Therefore, the remission rate in the anti-TNF arm is a conservative estimate.

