#### Outcome analyses

The safety population will include all patients who receive any trial treatment.

The modified intention-to-treat population for the primary analyses will include all patients who receive any trial treatment and who have a baseline joint assessment measurement and at least one further joint assessment post-baseline. No imputation of the primary outcome is planned for patients missing a 24-week assessment; instead, the trial sample size has been inflated to account for patient withdrawal. For the secondary endpoints, this includes all patients who receive any trial treatment and have available data for the respective outcome measure.

The intention-to-treat population includes all randomised patients in their treatment arms who have available data for the respective outcome measure.

Glucocorticoid-free arthritis remission rate at 24 weeks will be calculated for each treatment arm by dividing the number of patients reaching the response criteria by the total number of patients randomised to each arm. Failures in glucocorticoid-free arthritis remission recorded prior to the 24-week outcome (eg, due to early initiation of biological DMARD trial) will be used in this assessment. Where patients are missing the primary outcome (eg, because their Week 24 assessment is missing), they shall be treated as a failure and included in the denominator only. In addition, the number of such patients in each arm will be reported. 95% CIs will be calculated for each rate.

The remission rate will be compared between arms using a χ^2^ or Fisher’s exact test. Moreover, we will use logistic regression models, adjusted for stratification variables and other baseline covariates deemed to be associated with the outcome (such as patient standard of care). This will allow us to present the treatment effect for each of the stratification variables, as well as attempt to distinguish efficacy effects relating to standard of care compared with those because of trial treatment.

Analyses of secondary and exploratory measures are included in online supplemental appendix 7.

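### The sample size removes the 10% who drop out but the analysis counts them as failures, so the stated 80% power is not tied to the analysis as written; calling 55% conservative is also not secured

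*Protocol article*

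**What the plan says.** Protocol article, Sample size calculation. With 80% power and a 5% significance level, the assumption is "21% remission rate in standard of care compared with 55% in the anti-TNF treatment arm". From this the section obtains a base requirement of 62 and then enlarges it, "with a 10% dropout allowance increasing the total trial size to 70 patients when rounded and split evenly between arms". The control rate comes from a local cohort. For the anti-TNF rate the section cites on-treatment remission in other arthritides: "Remission rates in established RA of 47% are seen at 6 months", then 60% in psoriatic arthritis (PsA) and up to 81% in early PsA. It argues that this population should do better than rheumatoid arthritis (RA) and resembles PsA more closely, and concludes: "Therefore, the remission rate in the anti-TNF arm is a conservative estimate".

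Protocol article, Outcome analyses. The paragraph on the modified intention-to-treat population says that a missing week 24 outcome will not be imputed and that the inflated sample size covers withdrawal instead. Two paragraphs later, the remission rate is defined with all patients randomised to the arm as denominator, and for those without the outcome "they shall be treated as a failure and included in the denominator only". The comparison uses a chi-squared or Fisher's exact test.

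**The concern.** Dividing by one minus the dropout rate preserves power only if dropouts are left out of both numerator and denominator, so that about 31 evaluable patients per arm remain at the assumed rates. If they stay in as failures, the number analysed does not shrink, but both rates do, and so does the difference between them. The sample size follows the first rule and the definition of the primary rate follows the second, while the outcome section states both. The 80% therefore describes an analysis other than the one the article defines.

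The label on the 55% compounds this. Readers told that the trial had 80% power under a cautious assumption will take a null result from 70 patients as stronger evidence against a worthwhile effect than it may be.

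**Working it through.** **Inputs.** From Sample size calculation: control 21%, anti-TNF 55%, 80% power, 5% significance, 62 inflated to 70, 10% dropout, benchmarks 47%, 60% and 81%. From Trial design: 35 per arm. From Outcome analyses: all-randomised denominator, missing counted as failure, chi-squared or Fisher. Sidedness is not stated; two-sided reproduces the article's figure.

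**1. The article's own figure.** Pooled-variance formula without continuity correction, mean rate 0.38:

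n per arm = [1.960·√(2·0.38·0.62) + 0.842·√(0.21·0.79 + 0.55·0.45)]² / 0.34² = [1.960·0.686 + 0.842·0.643]² / 0.1156 ≈ 30.8, so 31 per arm and 62 in total.

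Dropout: 62/0.90 = 68.9, made 70 to split evenly. Both figures reproduce; there is no arithmetic slip.

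**2. Missing counted as failure.** If 21% and 55% are rates among assessed patients (an assumption), 10% missing in each arm gives 0.9 × 21% = 18.9% and 0.9 × 55% = 49.5%. The difference falls from 34 to 30.6 points. The same formula then asks for 37 per arm, 74 in total.

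**3. Exact power.** Sum Bin(i; n, pA) × Bin(j; n, pB) over all tables (i, j) with two-sided p < 0.05.

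| Reading of the assumed rates | n per arm | Rates | Chi-squared | Fisher |
|---|---|---|---|---|
| As designed, dropouts removed | 31 | 21% v 55% | 80.9% | 73.0% |
| Rates among assessed, 10% failures in both arms | 35 | 18.9% v 49.5% | 79.4% | 71.7% |
| 21% already counts losses, only Arm B diluted | 35 | 21% v 49.5% | 72.4% | 63.9% |
| Both rates already count losses | 35 | 21% v 55% | 85.3% | 79.3% |

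With both arms diluted, the loss due to dropout is 80.9 − 79.4 = 1.5 points (chi-squared) or 73.0 − 71.7 = 1.3 points (Fisher). Most of Fisher's gap from 80% is already in the design at 31 per arm.

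Other dropout levels, both arms diluted, normal approximation (80.3% at 31 per arm): 5% gives 81.8%, 10% gives 78.2%, 15% gives 74.5%, 20% gives 70.5%.

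**4. The benchmarks.** As cited, 55% is above 47% and below 60% and 81%. Multiplying everything by 0.9, 49.5% is above 42.3% and below 54.0% and 72.9%. The ordering is unchanged.

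**5. Power over the benchmark range.** Exact chi-squared, 35 per arm. Undiluted, 21% v 47% gives 65.0% and 21% v 60% gives 92.8%. With 10% failures in both arms, 18.9% v 42.3% gives 57.8% and 18.9% v 54.0% gives 88.5%.

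**6. Detectable difference.** With 35 randomised per arm, 21% v 52.5% on the all-randomised scale gives 80.1% (chi-squared). With Fisher slightly more than 55% would be needed, since 21% v 55% gives 79.3%.

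**The case against.** The strongest reply is that the effect is negligible. On equal 10% dropout the chi-squared power is within a point of the target, and if the assumed rates already count losses it is above the target. That stands as far as size goes. It does not remove the contradiction, because the article does not say which reading applies, and on the last reading no dropout inflation was needed at all.

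On the label, the article does not present RA as the target. It gives reasons to expect more than the RA rate and prefers PsA, where both figures exceed 55%. That is a fair argument, and it means the word is not refuted.

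A reader might go further and infer that, once 10% dropout is applied, 55% exceeds two of the benchmarks, because 60% becomes 54.0%. The document does not support this. It discounts the benchmarks and leaves 55% alone, whereas the dilution argument itself needs 55% to be a rate among assessed patients. Even on that mixed basis the margin is one point and vanishes at dropout of 8.3% or less (1 − 55/60). Nor does the article say whether the benchmark rates exclude dropouts.

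A reader might also blame dropout for the 72% under Fisher or for the 58% at a 47% remission rate. The first is mostly a property of the test, the second mostly of the lower assumed rate.

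**Conclusion.** The inconsistency holds: the inflation rests on one rule for missing outcomes and the definition of the primary rate on another. Its size depends on an unstated fact, namely what the 21% and 55% count. Exact power for the 70 planned patients ranges from 72.4% to 85.3% (chi-squared) or 63.9% to 79.3% (Fisher) across the readings above, all at 10% missing. When both arms are diluted, the loss from dropout alone is small.

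The label is unsecured rather than wrong. The 55% exceeds the only RA figure, at which power would be 65% before any dilution, but it lies below both PsA figures.

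This is a reporting correction that should be made. It does not show that the trial is materially undersized.

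**What to change.** - In Outcome analyses, keep one rule. If missing counts as failure over all randomised patients, delete the sentence that says there is no imputation because the sample size was inflated.
- In Sample size calculation, state whether 21% and 55% count losses as failures.
- Restate the power for 70 randomised patients under that rule and the chosen test, and add the all-randomised difference detectable with 80% power (about 21% versus 52.5% with chi-squared).
- Delete the word conservative, or qualify it by giving power for anti-TNF rates from 47% to 60%.

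The cost is wording and, on most readings, a slightly less favourable stated power. Enrolment, treatment and data collection do not change.

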#### Subgroup and interim analyses

The main estimators will be adjusted for the stratification variables (see Randomisation section), with results presented for each stratum; no further subgroup analyses are planned. There are no planned interim analyses.

No formal stopping rules have been established; however, on recommendation of the independent data monitoring committee (DMC), trial stoppage may occur dependent on the results of an ad hoc interim analysis.

### Harms reporting and analysis

Adverse events (AEs) are measured by National Cancer Institute (NCI) Common Terminology Criteria for Adverse Events, V.5.0.^29^ Definitions of different types of AEs are listed in online supplemental appendix 8. The reporting period for AEs will be between the date starting trial treatment (Week 0) until Week 48.

Side effects are commonly encountered in patients receiving adalimumab, prednisolone or other anti-arthritic drugs that may subsequently be used in either arm of REACT. As the safety profiles of the drugs used in this trial are well-characterised, only adverse reactions (ARs), those harms that are related to the arthritis interventions, will be reported together with new IrAEs. All ARs will be reported using electronic case report forms (eCRFs). However, all AEs that meet the definition of a serious adverse event (SAE; see online supplemental appendix 8) even if they are unrelated to the arthritis interventions will be reported.

Respiratory and systemic non-opportunistic infections are very common and are recognised ARs with adalimumab and glucocorticoids. Hospitalisations for these events may be completed on an expected serious adverse reaction form and do not require expedited reporting.

Any death occurring during the protocol defined follow-up period, whether considered related or not, must be reported as an SAE within 24 hours of the investigator becoming aware of the event.

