### Trial design

REACT is a prospective, multicentre, open-label, superiority, two-arm, randomised controlled clinical trial to guide initial therapy for patients with ICI-IA. The trial will compare the current standard of care (prednisolone; Arm A) to adalimumab without glucocorticoids (Arm B) (figure 1). REACT aims to recruit 70 patients (35 in each arm) from >10 UK hospitals.

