### Tissue and blood samples

A sub-study will collect serum and whole blood at screening and Week 12, as well as optional ultrasound-guided synovial tissue biopsies at selected centres pre- (Week 0) and post-intervention (Week 12). Consent for participants is optional for synovial biopsy and baseline DNA collection.

Biopsy samples in formalin will be shipped to the University of Birmingham for paraffin embedding and storage. Blood samples will be processed for sera at site and stored frozen together with whole blood for DNA and RNA and whole blood in Cytodelics mix before shipment in batches to the University of Birmingham.

All samples will be collected in accordance with national regulations and requirements including standard operating procedures for logistics and infrastructure. Samples will be taken in appropriately licensed premises, stored and transported in accordance with the Human Tissue Authority guidelines and National Health Service (NHS) trust policies.

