Placebo use would have been necessary in each arm ie, one arm would have placebo anti-TNF, and the other placebo glucocorticoids. This would increase patient burden, particularly if subsequent therapies need to be added and considering the background cancer diagnosis.Placebo glucocorticoid would pose particular problems as this would need to be titrated down in accordance with usual clinical practice with a view to stopping. In our experience, it is relatively common for a patient who was initially doing well to flare on glucocorticoid reduction and therefore this would lead to a high rate of unblinding. Further, if the 20 mg dose of prednisolone is chosen and there is no initial response, a common clinical strategy would be to escalate to 40 mg.In the anti-TNF arm, if a patient responded but still had low activity, then consideration could be given to adding methotrexate or hydroxychloroquine, alongside the anti-TNF injection and the placebo glucocorticoid. If the patient only partially responded or non-responded, then glucocorticoid therapy may be considered clinically appropriate. However, not knowing which arm the patient was in would necessitate unblinding.Were the patient to develop another IrAE requiring systemic treatment during the trial, this would also necessitate unblinding, since glucocorticoids are typically first-line management.

Another major strength of the trial is the development of a specific patient-centred ranked composite outcome, co-produced with our patient partners, increasing the relevance of the trial results to the patient population. REACT represents one of the first trials in ICI-IA; therefore, how patients and clinicians would prioritise oncological, rheumatological and quality of life outcomes is currently unknown. The aim is to incorporate a patient’s overall status and treatment response and allow patients to inform the analyses performed. The ranking will be via consensus among clinicians and patients, informed by a literature review of all published trials and studies in ICI-IA and clinical trials of ICI, a focus group incorporating patient partners, rheumatologists and oncologists and a survey. Ultimately, this will allow us to retrospectively rank all patients according to the desirability of their overall status and compare their position between treatment arms.

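### Non-serious harms other than new IrAEs are recorded only if judged related to the arthritis treatment, so in this open-label trial their between-arm comparison mixes event rate with unblinded attribution

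*Protocol article*

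**What the plan says.** All references are to the protocol article.

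- **Blinding** (Trial design): "REACT is a prospective, multicentre, open-label, superiority, two-arm, randomised controlled clinical trial". The article describes no blinded or central review of causality.
- **Non-serious harms** (Harms reporting and analysis): "only adverse reactions (ARs), those harms that are related to the arthritis interventions, will be reported together with new IrAEs". The reason given, that the safety of the trial drugs is already well known, stands at the start of the same sentence: "As the safety profiles of the drugs used in this trial are well-characterised, only adverse reactions (ARs), those harms that are related to the arthritis".
- **Serious harms** (same section): all events meeting the definition of an SAE are reported, "even if they are unrelated to the arthritis interventions will be reported".
- **Deaths** (same section): "Any death occurring during the protocol defined follow-up period, whether considered related or not, must be reported as an SAE".
- **Window** (same section): "The reporting period for AEs will be between the date starting trial treatment (Week 0) until Week 48".
- **Biopsy** (Tissue and blood samples): the sub-study includes "optional ultrasound-guided synovial tissue biopsies at selected centres pre- (Week 0) and post-intervention (Week 12").

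Definitions of the types of adverse event are in supplemental appendix 8, which is not shown.

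**The concern.** Relatedness is usually a property recorded about an event. Here, for one class of harms, it decides whether the event is recorded at all. The class is non-serious events that are not new IrAEs, and whoever makes the judgement knows the arm.

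Attribution is also hard in these patients. They have cancer, are receiving or have recently received an ICI, and may in either arm go on to prednisolone, conventional DMARDs or a biological DMARD. A non-serious infection or an episode of fatigue can have several plausible causes. If investigators resolve that doubt differently in the two arms, the recorded rates differ for that reason alone.

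A drug's known profile in other arthritides tells the investigator what to look for. It does not supply a fair comparison of the two strategies in this population, and the Discussion itself says that "REACT represents one of the first trials in ICI-IA". What is at stake is the randomised comparison of lower-severity harms, as seen by the DMC and in the final report. Events that were filtered out are not in the dataset, so no analysis can correct for the filter.

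**Working it through.** **Plan figures.** The article gives no expected harm rate and no attribution rate, so there is no harms figure to reproduce. The only design figure used below is 35 patients per arm (Trial design). It serves only to turn rates into patients.

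**Which harms pass through the relatedness filter?**

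| Type of harm | Must it be judged related to the arthritis treatment to be reported? |
|---|---|
| Death | No |
| SAE | No |
| New IrAE, non-serious | No, although calling it immune-related is also an unblinded judgement |
| Other non-serious event | Yes |

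The concern is confined to the last row.

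**Formula.** Assume at most one event of a given kind per patient. Let p be the true proportion with the event and a the probability that it is judged related. Then

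recorded proportion = p × a

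and the recorded ratio, Arm B to Arm A, is (p_B / p_A) × (a_B / a_A). If the true rates are equal, the first factor is 1 and the recorded ratio is the ratio of attribution probabilities alone.

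**Illustration, all inputs assumed.**

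- Equal true rates of 40% (14 of 35 in each arm), attributed 80% in Arm B and 40% in Arm A: 0.40 × 0.80 = 0.32 and 0.40 × 0.40 = 0.16. The record shows 32% v 16%, or 11.2 v 5.6 expected patients of 35: a 16-point, two-fold excess with no true difference.
- True rates of 40% in Arm B and 20% in Arm A, attributed 40% and 80%: 0.40 × 0.40 = 0.16 and 0.20 × 0.80 = 0.16. A true two-fold excess is recorded as no difference.

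**Range, with equal true rates in both arms.**

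| True rate | Attribution A, B | Recorded A, B | Difference (B − A), points | Ratio (B / A) |
|---|---|---|---|---|
| 40% | 50%, 50% | 20%, 20% | 0 | 1.00 |
| 40% | 50%, 70% | 20%, 28% | 8 | 1.40 |
| 40% | 40%, 80% | 16%, 32% | 16 | 2.00 |
| 60% | 50%, 70% | 30%, 42% | 12 | 1.40 |
| 60% | 40%, 80% | 24%, 48% | 24 | 2.00 |
| 60% | 70%, 50% | 42%, 30% | −12 | 0.71 |
| 80% | 50%, 70% | 40%, 56% | 16 | 1.40 |
| 80% | 40%, 80% | 32%, 64% | 32 | 2.00 |

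Over these assumed inputs the spurious difference runs from 0, when attribution is the same in both arms, to 32 points. Exchanging the attribution probabilities between the arms reverses its sign. The table shows what the rule permits, not what is likely.

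**The case against.** The strongest defence is that this is a deliberate, openly reasoned choice for a pragmatic trial of 70 patients on established drugs, and that the most serious harms are protected. That largely stands. Deaths and SAEs are counted whatever their cause, new IrAEs have their own route, and other IrAEs are a key secondary outcome. The point is therefore a design weakness in one part of the harms data, not a contradiction or an error.

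Several stronger readings are tempting, and the document does not support them.

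- **The whole harms comparison is unreliable.** A reader who stops before the mention of new IrAEs might infer this. The table of harm types shows that it does not follow.
- **Infection will be over-attributed to adalimumab.** The harms section names respiratory and systemic non-opportunistic infections as recognised reactions to both adalimumab and glucocorticoids, which pushes attribution the same way in each arm. It does not make every non-serious infection reportable, so the filter remains, but no direction of bias can be predicted.
- **A cancer-progression signal could be lost.** The Discussion mentions a retrospective suggestion of earlier progression with anti-TNF. Cancer response and overall survival are separate outcomes and do not depend on this filter.
- **Adalimumab is untried in this setting.** The Introduction places anti-TNF in the existing treatment sequence and reports its use in refractory disease. What is new is its use as initial therapy.
- **Filtered events are lost entirely.** Participants keep a daily diary with room for side effects, which sites collect and check (Treatment compliance). Some trace may survive, but nothing in the article makes those entries reportable events.
- **Non-serious biopsy harms are excluded.** On the wording shown, such a harm is not related to an arthritis intervention, and one arising before the first dose would precede the reporting window. That is an inference: appendix 8 or the full protocol may cover procedure-related events. A serious complication within the window is already reportable as an SAE.

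**Conclusion.** The point holds for non-serious harms that are not new IrAEs, and only for those. For them, an unblinded relatedness judgement decides entry into the data, so following the plan exactly leaves their between-arm comparison open to differential attribution that cannot be undone at analysis. The size and direction are unknown, because the documents give no event or attribution rates; the 32% v 16% example rests wholly on assumed values. The conclusion also assumes that no blinded causality review is set out in documents not shown. The biopsy matter is a query, not a finding. Overall this is a cheap improvement: it changes no stated figure and does not touch the primary outcome.

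**What to change.** In the harms section, for both arms over the existing reporting period, record regardless of attribution:

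1. all infections;
2. all grade 3 or higher adverse events;
3. all adverse events leading to interruption or stopping of arthritis therapy or ICI.

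Keep relatedness as a field on the form. Present the all-cause comparison of these events as the main harms table, with the related-only comparison beside it. Leave the rules for SAEs, deaths and new IrAEs as they are. Recruitment opened in February 2025, so collection would change mid-trial: report the amendment date and show which events were collected under each rule.

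Separately, confirm that appendix 8 or the full protocol makes non-serious synovial biopsy harms reportable from the time of the procedure, and add this if not.

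The cost is a protocol amendment and modestly more eCRF entry for 70 participants. No new visits are needed, since participants are already in regular contact with the teams and their diaries are already checked at scheduled visits. The sponsor's reason for light reporting is respected: unrelated grade 1–2 non-infectious events that change no treatment stay exempt. The remedy is therefore partial. Attribution would still filter those lower-grade events, and knowledge of the arm could still affect which symptoms are mentioned and how they are graded.
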